#### Weights and blood pressures

Weight and blood pressure (BP) readings will be monitored at baseline and then at each subsequent dialysis visit. These will be measured pre- and post-dialysis. Inter-dialytic weight gain (IDWG) or loss will be recorded. BP readings taken during dialysis (intra-dialytic BPs) will also be recorded.

#### Blood tests

In routine dialysis practice, the drawing of ‘monthly bloods’[26] involve regular measurements of full-blood count (FBC), serum biochemical profile (BCP) and C-reactive protein (CRP), and 3-monthly measurements of serum Ferritin, Transferrin Saturations (TSAT) and Parathyroid hormone (PTH) levels. We will utilise these routine tests when making selected comparisons between patients in the two treatment arms (see outcomes). Bloods samples are drawn at the first dialysis session of each calendar month. Urea reduction ration (URR) and eKt/V_urea_ are calculated monthly using the pre- and post-dialysis serum urea levels [27].

Additional (non-routine) pre-dialysis BCP testing will be carried out on days 7, 10 and 14 of dialysis to ensure close monitoring of serum potassium levels during the first 2 weeks of treatment.

#### Urine collections and estimation of RRF

Serial 24-h interdialytic urine collections will be used to monitor RRF. Proportion of patients completing 24-h urine collections and urine volumes will be recorded. Renal urea clearance (KRU) will be estimated from the rate of urea excretion and time-averaged serum urea concentration change during the collecting interval using method described by Obi et al. [28].

Cystatin C levels will be measured pre-dialysis at baseline, 1, 3 and 6 months. There is controversy on whether Cystatin C alone adequately predicts GFR (or RRF) in *established* dialysis patients [29]. Its role in estimating GFR in new HD starters remains unexplored and the current study presents a unique opportunity to correlate RRF estimates from Cystatin C levels and urine collections over the first 6 months of dialysis.

#### Bio-impedance spectroscopy and fluid load

Bio-impedance spectroscopy (BIS) will be performed using Body Composition Monitor (Fresenius Medical Care, Germany) [30, 31]. Readings will be taken immediately pre-dialysis with patients reclined at 30 degrees [32] and electrodes placed on patient’s arm and foot on the same side of the body avoiding the vascular access side [33]. N-terminal pro-Brain type natriuretic peptide (NT-proBNP) levels will be measured at regular intervals to evaluate the impact of incremental HD on cardiac load [34, 35].

#### Quality of life and functional status

Quality of Life will be measured using the Kidney Disease Quality of Life Instrument-Short form (KDQOL-SF)™ v1.3 questionnaire [36] and performance status using the Karnofsky performance index [37, 38]. These will be performed at baseline and then repeated at 3 and 6 months. All tests, except 24-h urine collections, will be completed within the designated dialysis slot and will not require additional hospital visits or prolongation of hospital visits.

#### Safety and adverse events data

There are several safety measures built-in to our incremental HD program to protect patients from the deleterious effects of a rapid decline in RRF around the time of dialysis initiation or when at least three-times weekly dialysis is needed from the start. First, we are only recruiting patient with planned out-patient dialysis start; this excludes the majority of those who develop critical or life-threatening issues related to CKD-5. Furthermore, all participants are reviewed at the start (see study procedures in supplementary table S1) to ensure safety before patients commence the program. During the program, patients receive regular visits from the study team (in the first month, five study related checks are undertaken including review by the study medic on four occasions). Also, clinicians can change the dialysis schedule e.g., offer extra dialysis or to take the patient off the program completely at any point during the study; for this reason, the mid-week dialysis slot is always kept open in case a participant needs additional dialysis. Finally, this a short incremental regime lasting just over 3 months; hence, a decline in RRF is anticipated and treatment increases are pre-emptive in this program.

Information related to adverse events (AEs) and serious adverse events (SAEs) will be recorded continuously throughout the study based on definitions presented in supplementary table S2. Routinely, all dialysis treatments are recorded in the local dialysis treatment database and a named nurse documents a narrative account of that day’s treatment making notes of any significant events. This information will be accessed by the study team and interrogated for AEs and SAEs and substantiated with information documented elsewhere in patients’ electronic health records. Compliance with the programme and adherence (or deviations) to the prescription will be monitored.

Intra-dialytic hypotension is common and affects 17% of all dialysis sessions [39]. We define IDH in accordance with the European Best Practice Guidelines [40] as a symptomatic drop in BP during dialysis of ≥ 20 mmHg in systolic or ≥ 10 mmHg in mean arterial pressures, requiring nursing interventions such as the stopping of ultrafiltration, administration of saline or moving patients to Trendelenburg position. IDH events are recorded in the nursing entries as above which will be used as a basis for coding this information.

### Primary outcome

The primary outcome of this study is recruitment. We aim to recruit 20 patients over 18 months. Data will be kept on the number screened, proportion eligible, proportion consenting and proportion completing the study.

#### Justification for primary outcome measure

Ultimately, the aim of this feasibility is to pave the way for a future RCT. In the planning of such a RCT, estimates of patient recruitment and adherence ratios are necessary as it affects resource allocation [41]. We would consider an acceptance ratio of ≥ 40% (i.e., the proportion of patients enrolled from all those eligible and approached for the study) and retention rate of ≥ 70% (i.e., participants completing the study) to indicate feasibility. Additional HD sessions for clinical needs do not affect the retention rate as these are considered part of therapy regime along with other key safety indicators.

### Secondary outcomes

The secondary outcomes of this study are grouped in to following sub-categories:

A. Safety outcomes

To compare key indicators of patient wellbeing in those receiving incremental HD and conventional care over the 6-month follow-up period:Differences in mean pre-dialysis BPs and IDWG (or loss)Comparison of pre-dialysis potassium levels, serum albumin, PTH, adjusted calcium and phosphate levels.Numbers of AEs and SAEs (based on definitions in table S2)Numbers of hospitalisationsNumbers and rates of major adverse cardiovascular events (the 4p-MACE: a composite of cardiovascular deaths, nonfatal myocardial infarctions, nonfatal strokes and hospitalisations for unstable angina) [42]Numbers and rates of all-cause mortalityAnaemia management: differences in Hb, Ferritin, TSAT and doses of IV iron and erythropoietin stimulating agent (ESA.)

B. Mechanistic outcomes

To study changes in RRF, fluid load, performance status and quality of life over 6 months in patients receiving incremental HD (incremental HD group only). All these are relative to baseline:Change in RRF using urine volume, KRU and Cystatin C levelsChange in pre-dialysis fluid load as measured using BIS and Ntpro-BNPChange in KDQOL-SF v1.3 scores (including in its sub-domains)Change in Karnofsky performance index

C. Qualitative outcomes

To explore patients’ experiences of starting HD incrementally and of participating in the current study using semi-structured interviews—see interview sub-study section.

D. Further feasibility outcomes

To acquire data needed for planning a future RCT:Progression to HD: some patients recruited for the current study may not start HD within the study period (the timing of onset of dialysis can be unpredictable). Of the patients recruited from pre-dialysis clinics, the proportion of patients progressing to receiving incremental HD within the study period will be reported. This will inform the number of additional participants needed in a future RCT and the duration of recruitment period.Completion rates of the non-routine tests namely the 24-h urine collections, BIS and the KDQOL-SF v1.3 questionnaire.

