### Recruitment

#### Recruitment for the intervention arm

Participants will be approached at the specialist pre-dialysis clinics or the dialysis unit with the participant information sheet (PIS). They will be given at least 24 h to consider the information. Following this, the investigator will meet patients in person to address their questions and obtain written informed consent if they show willingness to proceed. They will remain in-active in the study, and under follow-up with their usual care providers, until the decision is made to start HD by their caring physician. The timing of HD initiation will be made independently of the study investigators by the clinical care teams, based on clinical needs and in consultation with patients and their relatives. Clinicians will not be blind to patients’ participation in the study; some pre-dialysis CKD-5 patients may have already signed up for the study prior to commencing dialysis. Whether the knowledge of patients’ interest in incremental HD influences decisions about the timing of starting HD is not known. The starting eGFRs will be reported for both incremental and control arm patients which could help address this current knowledge gap.

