#### Recruitment for control arm (historical controls)

Each participant in the incremental HD arm of the study will be matched with 2 patients who had previously received the conventional HD treatment (historical controls; matching ratio 1:2). Participants for the control arm will be identified using the local dialysis treatment database. All patients starting HD therapy since 2013, the inception date of the database, will be included in the searches. Their dialysis treatment data (including nursing notes and exceptions), along with details of their medical history will be extracted for further analysis (see below).

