### Analysis

The findings will be reported in accordance with the Consort Statement for Pilot and Feasibility trials [43]. A consort flowchart showing the number of patients screened, approached for participation, consented and those who eventually started treatment will be presented.

Patient follow-up period will be split in to the four phases of incremental HD regime (see Fig. 2 for phases of incremental HD). Details of dialysis treatments delivered in each phase to participants in both treatment arms will be expressed in sessions/week (frequency), minutes/week (duration), mean monthly URR and median sessional eKt/V_urea_ as well as OCM Kt/V_urea_. Given that patients in conventional HD group (historical controls) will have had more BPs and weight measurements recorded since they were on three-times weekly dialysis from the outset, their mid-week BP and weight measurements will not be used in computing these averages (to avoid regression towards mean). Weights, BPs and IDGW will be summarised as means (and SDs) for each treatment phase.

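### The safety comparison is worded around patients who receive incremental HD after a pre-programme safety review not stated for controls; if anyone is held back, deaths, 4p-MACE and hospitalisations can look better with no true effect

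*Protocol article*

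**What the plan says.** The protocol article describes the two groups as follows.

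- **Comparison.** Secondary outcomes, part A, sets out "To compare key indicators of patient wellbeing in those receiving incremental HD and conventional care over the 6-month follow-up period". The Abstract likewise describes the 20 patients as people who begin HD on the twice-weekly schedule.
- **Route into the incremental group.** Under Recruitment for the intervention arm, consent may come before dialysis: "They will remain in-active in the study, and under follow-up with their usual care providers, until the decision is made to start HD". Under Safety and adverse events data, "we are only recruiting patient with planned out-patient dialysis start; this excludes the majority of those who develop critical or life-threatening issues", and then "all participants are reviewed at the start (see study procedures in supplementary table S1) to ensure safety before patients commence the program". That section presents these measures as protection against, among other things, a need for at least three sessions a week from the outset. After the start, clinicians may also "take the patient off the program completely at any point during the study".
- **Route into the control group.** "All patients starting HD therapy since 2013, the inception date of the database, will be included in the searches". No equivalent review or entry filter is stated.
- **Matching.** A propensity score on 14 variables, with nearest-neighbour matching, no caliper and no replacement. The variables include albumin, CRP, creatinine, access type, blood pressure and cardiovascular history. They do not include potassium, fluid status, urine output, planned start or recent myocardial infarction.
- **Reporting.** Events are given for both arms without formal tests. The flowchart counts those "consented and those who eventually started treatment".

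**The concern.** A review meant to ensure safety before a reduced schedule begins can, in principle, conclude that a participant should not begin it. Someone who consented and starts HD on another schedule is then not among those receiving incremental HD. Read literally, the objective leaves that person out of the incremental group before follow-up begins. Comparable patients in the historical records stay in the control pool, because nothing stated removes them.

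Applying Table 1 to the controls would make the groups more alike, but it cannot reproduce a clinical judgement made after consent. Matching helps only as far as the 14 variables carry the reasons for that judgement. Potassium and fluid status, which the regime itself monitors for safety, are not among them.

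At stake is the use the article gives the control arm. The Discussion says it is needed to compare rates of pre-defined safety events, and the Analysis section says descriptive comparisons will be examined for signals. A one-sided selection could mask a modest harm signal or suggest a benefit that is not there.

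**Working it through.** **The plan's own figure.** 20 participants × 2 controls each = 40 controls, as stated under Sample size. There is no power calculation to reproduce.

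**Assumed inputs (none is in the article).**
- h: share of consenters starting HD who are held back; 0, 5%, 10% or 20%.
- k: their event risk relative to the other starters; 2 or 3.
- p: event risk among all starters; 10% or 30%, needed only for absolute figures.
- m: share of the selection that matching removes; 0, one half or all.

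**Formula, no treatment effect.** Let r be the risk among those not held back. Then p = r(1 − h) + r·k·h, so r = p/(1 − h + hk). If matching corrects nothing (m = 0), the control risk is p and the apparent risk ratio is RR = r/p = 1/(1 − h + hk). If matching removes half (m = 0.5), the control risk is (p + r)/2 and the ratio becomes 2RR/(1 + RR).

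| h | k | 1 − h + hk | RR, m = 0 | RR, m = 0.5 |
|---|---|---|---|---|
| 0 | any | 1.00 | 1.00 | 1.00 |
| 5% | 2 | 1.05 | 0.95 | 0.98 |
| 10% | 2 | 1.10 | 0.91 | 0.95 |
| 10% | 3 | 1.20 | 0.83 | 0.91 |
| 20% | 2 | 1.20 | 0.83 | 0.91 |
| 20% | 3 | 1.40 | 0.71 | 0.83 |

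With m = 1 every ratio is 1.00.

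**Against random error.** The standard error of a risk difference is √[p(1 − p)(1/20 + 1/40)].
- p = 10%: √(0.09 × 0.075) = 0.082, or 8.2 points. The largest bias in the table is 10% − 10%/1.40 = 2.9 points.
- p = 30%: √(0.21 × 0.075) = 0.125, or 12.5 points. The largest bias is 30% − 30%/1.40 = 8.6 points.

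**Opposite force on adverse event counts.** The incremental arm has five study checks in the first month, four of them with a study medic. Recording 1/RR times as many events would cancel the m = 0 bias: 1.05 times (h = 5%, k = 2) to 1.40 times (h = 20%, k = 3). Such an offset is plausible for adverse events and unlikely for deaths.

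**Dilution if all consenters who start HD are analysed.** Those on the regime contribute (1 − h)/(1 − h + hk) of the expected events, so this is the fraction of any relative excess from harm that would remain visible: 0.95/1.05 = 90% (h = 5%, k = 2) to 0.80/1.40 = 57% (h = 20%, k = 3).

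**The case against.** Several parts of the opposing case stand.

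- **A reader might infer that the sickest consenters are held back on the day of starting.** The article does not say this. It gives a review at the start and its purpose, and refers to a supplementary table that is not shown. It states neither what follows an unfavourable review nor that anyone fails it. An unwell starter may also stay in the arm, because extra sessions are allowed and do not count against retention.
- **A reader might infer that the plan fixes an as-treated analysis set.** It does not. The phrase stands in an objective, the Analysis section speaks only of both arms, and analysis sets are often left to the SAP or full protocol. What can be said is narrower: the stated wording points to recipients, and an SAP that follows it literally would omit anyone held back.
- **A reader might cite the progression measure**, by which "the proportion of patients progressing to receiving incremental HD within the study period will be reported". That item concerns the unpredictable timing of dialysis, not people who start HD on another schedule, so it is not evidence here.
- **A reader might conclude that every safety outcome is biased in favour of incremental HD.** Matching on predictors of mortality removes an unknown part of the selection, and closer monitoring can raise adverse event counts in the incremental arm.
- **Little depends on it formally.** Feasibility is judged on acceptance (at least 40%) and retention (at least 70%), secondary outcomes are descriptive, and random error exceeds the bias.

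None of this supplies the controls with an equivalent review, or shows that the 14 variables capture its result. The flowchart gives counts, not the outcomes of people held back.

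**Conclusion.** The concern holds in a conditional form. The incremental group passes a pre-programme safety review that controls are not stated to have passed, and the matching variables do not fully capture it. If any consenter starts HD but is held back, the comparison of deaths, 4p-MACE and hospitalisations can favour incremental HD under no effect. The illustrative null risk ratio is 0.71 to 0.95 before matching (h = 5% to 20%, k = 2 to 3), 0.83 to 0.98 if matching removes half the selection, and 1.00 if nobody is held back. For adverse event counts the net direction is uncertain. The values of h, k, p and m are assumptions, and the article allows h = 0. Because the comparison is descriptive and small, this is an improvement to consider, not a flaw that undermines the study.

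**What to change.** In Secondary outcomes part A and in the Analysis section, report the comparison with controls as two lines, side by side:

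1. all consenters who start HD in the study period, whatever the result of the start review or any later removal from the programme, with controls matched to all of them and outcomes taken from the routine database;
2. those who received incremental HD.

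Report the number held back at the start review, the reasons and their outcomes, separately from consenters who never started HD. Apply the Table 1 entry criteria to the control pool as far as records allow: planned start, prior renal follow-up, no recent myocardial infarction and no cross-over from peritoneal dialysis. Neither the review nor the regime changes.

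**Cost.** Mainly wording. Those held back have already consented, and most of the outcomes are routine records, so no visits are added. If 20 are to receive the regime, 20/(1 − h) rounded up gives 22, 23 or 25 starters for h = 5%, 10% or 20%, and so 44, 46 or 50 controls instead of 40. If nobody is held back, the two lines coincide.

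**Downside.** Conventionally treated patients dilute line 1, slightly if few are held back and more if many are, while line 2 carries the selection. Neither line should be read alone for harm.

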### The intervention (the incremental HD regime)

Participants in the intervention group will receive incremental HD using a novel approach, starting therapy on twice-weekly basis with progressive increases in the duration and frequency of sessions over 15 weeks, achieving conventional treatment times by the end of this period.

The treatment delivered will comprise of a ‘start’ phase, representing just the first 2 days of dialysis (this is similar to conventional start), followed by 3 incremental phases or steps (also see Fig. 2):Start (phase 1): (first 2 days of HD): day 1, 2-h HD session; day 2, 3-h HD session.Phase 2: twice-weekly 2-h long dialysis sessions for 2 weeks.Phase 3: twice-weekly 3-h long dialysis session for 6 weeks.Phase 4: three-times weekly 3-h long session for 6 weeks.

Following this, participants will continue long-term HD as per clinical requirements. The regime includes several safety elements including frequent fluid status monitoring (through clinical examinations and bio-impedance analyses) and regular potassium testing. Clinicians and dialysis nurses can override the regime at any point if clinically indicated.

The regime tested here has been developed by the study investigators ([name], SB) in consultation with patient groups as a pragmatic way of reducing exposure to dialysis during the critical early transitional period. At the designing stage, patient engagement involved discussions with National Institute of Health Research (NIHR) patient research ambassadors for renal medicine at our centre and the members of Hull Kidney Patients Association (HKPA). In addition, a brief questionnaire was given out to 20 current HD patients to gauge their opinions on the current proposals. Patient feedback was very positive; patients particularly appreciated the focus on maintaining independence at the start of HD which they valued highly. HKPA members saw this as a much-needed advancement in dialysis therapies and felt that patients will be motivated to help. The group gave positive suggestions on how to narrow down the process of identifying potential participants e.g., by prioritising the sub-set of patients who were being referred for vascular access procedure (as they are the most likely patients to start dialysis soon). In the survey of 20 HD patients, 10 patients responded 7 of whom indicated that they would have taken part in the study if they had the opportunity.

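### In Phases 2 and 3, mean interdialytic weight gain is compared over gaps about 1.4 to 1.5 times longer in the incremental arm, and the mid-week exclusion does not correct this

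*Protocol article*

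**What the plan says.** Secondary outcomes, part A (safety), names as a comparison between the incremental and conventional arms over 6 months "Differences in mean pre-dialysis BPs and IDWG (or loss"). The section on weights and blood pressures says "Inter-dialytic weight gain (IDWG) or loss will be recorded". The Analysis section adds "Weights, BPs and IDGW will be summarised as means (and SDs) for each treatment phase". None of the three gives a unit, a per-day version or a percentage-of-weight version.

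The intervention section sets Phase 2 as "twice-weekly 2-h long dialysis sessions for 2 weeks", Phase 3 as "twice-weekly 3-h long dialysis session for 6 weeks" and Phase 4 as "three-times weekly 3-h long session for 6 weeks". The Analysis section describes controls as having more readings "since they were on three-times weekly dialysis from the outset". For that reason it leaves the controls' mid-week blood pressures and weights out of the averages. The reason given is the number of readings and regression to the mean; gap length is not mentioned. Secondary outcomes get no formal tests and are compared descriptively to look for signals.

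**The concern.** IDWG is the weight put on between the end of one session and the start of the next, so it grows with the time between them. For 8 weeks the two arms have different planned gaps. A higher mean IDWG in the incremental arm during those weeks has two possible sources: more days of accumulation, or faster accumulation per day. The planned summary cannot separate them.

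The article recognises that unequal session frequency affects these averages and fixes a rule for it, but that rule addresses which readings are counted, not how many days each gain covers. With no test or model, the descriptive difference is what readers will interpret, and the article says the data will be used to design the regime for a future randomised trial. A longer gap could be mistaken for poorer fluid control, or a lower daily gain in the incremental arm could be hidden.

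**Working it through.** The article gives no IDWG figure, unit or assumed variance, so there is nothing of its own to reproduce. The check is gap arithmetic on the stated schedules.

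**Inputs from the article.** Incremental arm: 2 sessions/week in Phases 2 and 3 (2 + 6 = 8 weeks), 3 sessions/week in Phase 4. Controls: 3 sessions/week throughout. Follow-up: 6 months, taken as 26 weeks. Targets: 20 incremental patients and 40 controls.

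**Inferred.** The safety section keeps the mid-week slot free for incremental patients, which implies gaps of 4 and 3 days when they dialyse twice weekly. Three sessions in a 7-day week imply gaps of 2, 2 and 3 days. The figure showing the regimen is not available to confirm this.

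**Mean gaps**
- Incremental, Phases 2 and 3: (4 + 3)/2 = 3.5 days
- Controls, all gaps: (2 + 2 + 3)/3 = 2.33 days
- Controls, mid-week reading dropped: (3 + 2)/2 = 2.5 days

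**Ratio of mean IDWG at equal daily gain** (gain proportional to gap length)
- All control gaps: 3.5/2.33 = 1.50
- Mid-week dropped: 3.5/2.5 = 1.40

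The exclusion therefore lowers the ratio from 1.5 to 1.4. By session, it leaves 3 v 3 days at the first session of the week, which is comparable, and 4 v 2 days at the last, a ratio of 2.0.

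**From Phase 4.** Under one reading rule for both arms the ratio is 1.0. If the exclusion is applied to controls only, it is 2.33/2.5 = 0.93, slightly reversed.

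**Size in kg, Phases 2 and 3.** Difference = r × (3.5 − control mean gap), where r is daily gain. The article gives no r, so 0.2 to 0.8 kg/day is an assumption.

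| r (kg/day) | Mid-week dropped (kg) | All control gaps (kg) |
|---|---|---|
| 0.2 | 0.20 | 0.23 |
| 0.4 | 0.40 | 0.47 |
| 0.6 | 0.60 | 0.70 |
| 0.8 | 0.80 | 0.93 |

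**Against sampling error.** With an assumed between-patient SD of 0.7 to 1.3 kg, SE = SD × √(1/20 + 1/40) = 0.19 to 0.36 kg. The schedule-only difference is then about 0.6 SE (0.20/0.36) to 4.9 SE (0.93/0.19, unrounded).

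**What could be hidden.** Equal per-gap means would occur if daily gain in the incremental arm were lower by 1 − 1/1.4 = 29% to 1 − 1/1.5 = 33%.

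**If pooled over 26 weeks**, with three-times-weekly dialysis assumed to continue after Phase 4 (8 twice-weekly weeks and 18 three-times-weekly weeks): with mid-week readings dropped for controls only, weighting by week gives [(8 × 3.5 + 18 × 2.33)/26]/2.5 = 1.08. Weighting by session gives [(16 × 3.5 + 54 × 2.33)/70]/2.5 = 1.04. Across the possible reading rules and weightings the range is about 1.04 to 1.20.

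**An ambiguity in the exclusion.** If the controls' mid-week weights are removed before IDWG is derived, the gain at the last session of the week would run from the first session across a dialysis treatment, and would not be an interdialytic gain at all.

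**The case against.** Four points can fairly be made for the plan.

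1. **The article states no unit.** How a secondary descriptive variable is derived is often left to the full protocol or analysis plan, neither of which is shown. This stands in part: a per-gap derivation is the natural reading of IDWG, but it is an inference. It does not dispose of the point, because the article does fix a rule for unequal frequency and that rule leaves a 1.4-fold difference in gap length.

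2. **The schedule is the intervention.** Weight carried into a session is a real safety exposure of less frequent dialysis, and dividing by days would remove it from view. This stands fully. Per-gap IDWG should remain, and a per-day measure should not replace it.

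3. **The affected period is short and visible.** Planned frequency differs only in Phases 2 and 3, results are shown by phase, and sessions per week are reported for both arms. Staff may also add sessions, so the nominal gaps are upper figures for some patients. This stands as a limit on size. Even so, seeing the frequencies does not give the reader the rate of gain.

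4. **No decision rests on IDWG.** Feasibility is judged on acceptance and retention, and no test is planned. This stands; no error rate is affected.

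A reader might also infer that a fall in IDWG on entering Phase 4 would be reported as a benefit of stepping up. The article does not support that: the within-arm change outcomes cover residual renal function, fluid load, quality of life and performance status, and not IDWG.

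**Conclusion.** The point holds for Phases 2 and 3. As the plan is written, a difference in mean IDWG in those phases cannot be read as a difference in rate of fluid gain, because the incremental arm's gaps are 1.4 to 1.5 times as long. The mid-week exclusion does not remove this and, if applied to controls only, tips the ratio to about 0.93 from Phase 4. The schedule-only difference is about 0.2 to 0.9 kg over 0.2 to 0.8 kg/day.

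This rests on gain proportional to gap length, the inferred 4/3 and 2/2/3-day patterns, a per-gap derivation, and the assumed range of daily gain.

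A reader might infer that the whole safety comparison of IDWG mainly measures the schedule. The documents do not support that. The frequencies differ for 8 of about 26 weeks, a pooled ratio would be only about 1.04 to 1.20, and even within Phases 2 and 3 the schedule's share depends on gain rates and SDs that the article does not give. This is a flaw of interpretation in a descriptive outcome, and a cheap one to repair.

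**What to change.** In Secondary outcomes (part A) and Analysis:

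- Keep IDWG per gap as the measure of fluid load before each session.
- Add IDWG per interdialytic day, defined as the gain divided by the days since the previous session, as a co-reported between-arm comparison by phase. Using actual session dates also handles extra sessions.
- State that each IDWG is derived from the immediately preceding session before any mid-week reading is excluded.
- Apply the same reading rule to both arms once both dialyse three times weekly.

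The local dialysis database records all treatments in both arms, so no new data are needed. The cost is one derived variable, a few sentences of analysis text, and two IDWG measures to interpret side by side. The per-day measure itself assumes roughly proportional accumulation, which should be said when it is reported.
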